# EVALUATION OF INTERVENTION EFFECTIVENESS (OBJECTIVES 1-5)

To achieve the first five objectives, we will test the effectiveness of five interventions included in the minimum package of adherence interventions using routinely collected data only. The interventions have been developed by the NDOH and will be implemented by the public sector clinics using their own staff and resources. Those interventions included in the evaluation were selected as having outcomes that could be assessed in a relatively short period of time, so that results can be used to refine the national guidelines and implementation. Below we detail each of the interventions and the populations we will use to evaluate the interventions.

We will use a matched cluster randomized design to evaluate the impact of each of the selected interventions. The National Department of Health, in consultation with the study team, will develop a short list of candidate primary health care clinics where early implementation of the package can occur. This short list will include proposed matched pairs of facilities which will be randomized to either implement the minimum package or not. Clinics will be matched on characteristics that are likely to affect study outcomes (patient volume, urban/rural location, current HIV viral suppression rate).

Because the interventions will be implemented clinic-wide and the evaluation will rely on routinely collected data only, we will include the entire patient population at each study site. All non-pregnant adult patients seeking HIV-related services at the study sites and eligible to receive one of the adherence interventions during the enrollment period will be included in the study through use of their clinic data. There will be no direct interaction with study subjects. Data will be collected from existing, routinely completed patient records, including clinic files, registers, cards, and databases. No additional data fields, beyond what are currently mandated under government guidelines, will be collected for the study. We assume that all study sites will follow the current guidelines for HIV care and treatment, dated December 2014[10] and the Primary Care 101 guide for TB, HIV, diabetes and hypertension care and treatment, dated 2013/14[15] as well as comply with the National Health Act of 2003.

Each of the interventions, while implemented as a package of services, will be delivered to a unique population within each clinic: patients newly eligible for ART, patients stable on ART, patients with poor adherence, and patients lost from care. (The exception to this is patients who are stable on ART and could be provided with either decentralized medication delivery or adherence clubs, but not both.) This will allow us to estimate the effect of each intervention individually, in the context of implementation of the overall minimum package. During the early stages of implementation of the Adherence Guidelines it is possible that eligible patients at intervention sites might not all be enrolled in an intervention they are eligible for. In order to ensure that this evaluation does not by chance exclude eligible patients who are exposed to the interventions, enrolment at intervention sites will include not only those eligible for the intervention but also eligible patients who receive the intervention.

The following five interventions will be evaluated under this protocol. Each is described in detail in the National Adherence Guidelines[11]. (Note: Additional details about primary and secondary outcomes, eligibility criteria, sample size, and data sources are included in later sections of this protocol.)

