## **b. Adherence Clubs**

Adherence clubs comprise adherent and stable patients on ART who meet at facilities or identified locations in the community, in groups of up to 30 patients every two to three months to receive group counseling, have a clinical assessment, and receive the required supply of pre-packed medications. Adherence clubs are managed by lay staff at the health care facility with support from community health workers. The goal is to keep patients engaged in care and adherent to their medication by providing social support and facilitating medication delivery and treatment monitoring, while also reducing patient visit burden on the clinics[13]. The adherence guidelines SOP provides detailed instructions for establishing and running the clubs and for eligibility criteria and data collection.

| *Primary outcome:* | Proportion of patients eligible for participation in an adherence club who receive all medications within the first 4 months after eligibility |
| --- | --- |
| *Eligibility:* | All adult patients who meet the criteria for being stable on ART (on same ART treatment regimen for at least 12 months; most recent viral load taken in past 6 months, 2 consecutive viral loads undetectable ) OR where a clinician confirms eligibility as a stable patient |
| *Sample size:* | 576 (288 per arm; 24 per cluster) |
| *Data sources:* | Tier.Net; pharmacy records; club register; other registers or records that document services provided during the period of club observation |

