- *Setting*. Both sites in each pair should draw from the same type of community: urban; informal settlement; or rural.
- *Location*. Pairs should be located relatively nearby one another, to facilitate data collection and increase similarity of the catchment populations.

- *HIV viral suppression*. The clinics in the pair should have ART patient viral suppression rates within 10% percent of one another (if data available).

Letters indicating Provincial and District Department of Health authorization to work at each study site have been obtained and are attached. The final number of clinics selected remains at 24 clusters.

In each pair, one clinic will randomly be assigned to receive early implementation of the minimum package of interventions, while the other will continue to provide standard of care. Randomization will be done through a random number generator in Microsoft Excel with a 1:1 ratio of allocation to intervention and control clusters.

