## **d. Data Entry and Storage**

During the enrollment period, which we anticipate to last for approximately six months, patients will be identified and enrolled from TIER.Net (Cohorts 1-5) and site records (TBHD cohort) consecutively until sample size targets are met. “Enrollment” will consist only of reviewing site records to select patients who have become newly eligible for the study in the previous interval; there will be no contact with patients for study purposes.

As explained above, the study will not generate any new data beyond what is called for by existing guidelines and procedures. To allow a valid evaluation, we will make efforts to ensure that the data the clinics are supposed to record are collected and documented completely and promptly. Study staff will visit the sites regularly to obtain electronic data sets, capture paper records and registers on electronic case report forms on dedicated tablets, and review data quality. If needed, study staff will assist the sites to complete all routine forms and records and enter them into a database. Once initial data collection systems are in place, we anticipate visiting each site at least every 10 days to collect data sets, review procedures, and respond to data queries from the previous visit. In order to ensure a secure transmission, the electronic data sets obtained from the clinic will be transferred from the study site via a dedicated secure VPN onto protected drives at the local office.

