## **c. Data Analysis Objectives 1-5**

Our general analytic plan will be the same for each of Cohorts 1-5. We will begin with descriptive analyses of the characteristics of each of the cohorts stratified by intervention/non-intervention (comparison) cohorts. We will also look for differences within the randomized matched pairs. Because the data will be collected as part of a clustered design, the data analysis will need to account for clustering. For each primary outcome described above, we will conduct a crude analysis comparing the proportion of subjects with the outcome in the intervention and comparison arms. Next we will conduct an analysis for each outcome accounting only for clustering using generalized estimating equations (GEE) with an unstructured correlation matrix and clustering by treatment site. In all cases the outcomes are dichotomous and therefore we will calculate relative risks comparing the intervention to the comparison arms using a log link function and a binomial distribution. Next, should any imbalances between treatment groups be detected, we will adjust for those covariates in our GEE model. Finally, we will look for differences in the effects of the strategies by important baseline characteristics (e.g. size of the treatment population, rural vs. urban, province, etc.) using stratified analyses.

We note that because each of the interventions is targeted at a different population with the exception of decentralized medication delivery and adherence clubs, which would not be delivered to the same people at the same time, we can estimate the impact of each intervention separately, as only one of them will be delivered to each cohort within a clinic at any one time. Since some patients may participate in more than one intervention (e.g. fast track initiation followed by tracing), we will conduct a sub-analysis restricted to those who received only one intervention to look for the effects of each intervention by itself.

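### Only intervention clinics may enrol patients because they received the intervention; with per-clinic quotas, this can bias the Objective 1–5 effects

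*Protocol*

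**What the plan says.** Clinics are allocated within matched pairs (section 8a): "Randomization will be done through a random number generator in Microsoft Excel with a 1:1 ratio of allocation to intervention and control clusters". Section 4 first describes full coverage: "we will include the entire patient population at each study site". It then anticipates incomplete uptake, noting that "it is possible that eligible patients at intervention sites might not all be enrolled in an intervention they are eligible for". So that exposed patients are not missed, it adds that "enrolment at intervention sites will include not only those eligible for the intervention but also eligible patients who receive the intervention". This last rule names intervention sites only.

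Section 9d describes something narrower than full coverage. Patients are identified from Tier.Net "consecutively until sample size targets are met". The targets in sections 4a–4e are 30, 24, 24, 42 and 24 per clinic for Objectives 1 to 5, at clinics with more than 1000 current ART patients (section 8a).

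The analysis in section 10c starts by "comparing the proportion of subjects with the outcome in the intervention and comparison arms", then fits GEE models, with adjustment for covariates found to be imbalanced.

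Two related passages matter less. Sections 4b and 4c admit stable patients by the listed criteria "OR where a clinician confirms eligibility as a stable patient", a route that the inclusion criteria in section 8b omit. Section 10c also says "we will conduct a sub-analysis restricted to those who received only one intervention to look for the effects of each intervention by itself".

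**The concern.** Randomising clinics makes the arms comparable only if patients then enter each arm by the same rule. Here receipt of the intervention is a way into the sample in one arm and cannot be in the other.

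Receipt is also close to several outcomes. Fast track counselling is meant to take two visits within a week, and its primary outcome is starting ART within 30 days. Club members collect their medication at club meetings, and the outcome is having received all medication. A patient taken in because he or she attended is partly selected on the result.

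The rule also works against what the protocol sets out to measure. Section 3c says that results will reflect implementation quality as well as efficacy, and Table 3 defines most primary outcomes among eligible patients. Incomplete uptake is therefore part of the effect, and over-representing recipients removes some of it. The estimates then feed the population weighting of Objective 6 and the cost per outcome of Objective 7. Adjusting for recorded covariates cannot be relied on to undo selection on attendance, and enrolling more patients under the same rule does not remove it.

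**Working it through.** **1. Does the rule change the sample?** If every eligible patient were enrolled, as section 4 says at one point, recipients would already be included and the rule would add nobody. Under a quota it can matter: a place taken by a patient who came in through receipt is a place not taken by the next patient in order of eligibility. The harm comes from the rule and the quotas together.

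**2. The plan's own figure (Objective 1).** Inputs from section 10b and Table 4: c = 12 clinics per arm, coefficient of variation k = 0.1, power 80%, alpha 0.05 (taken as two-sided), rates 0.60 and 0.75, inflation 20%. The usual cluster formula is

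c = a + q²·[p0(1−p0)/m + p1(1−p1)/m + k²(p0² + p1²)] / (p1−p0)²

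With t quantiles on 22 df, q² = 8.60 and a = 2:

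- (12−2)·0.15²/8.60 − 0.01·(0.36 + 0.5625) = 0.0169
- m = (0.24 + 0.1875)/0.0169 = 25.2
- 25.2 × 1.2 = 30.3 per clinic, against 30 stated.

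The variance model therefore matches the plan and can be used below.

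**3. Bias with no true effect.** Let f be the share of intervention-arm places shifted to receipt-selected patients, and d the outcome gap between them and the eligible patients they displace. Neither is in the protocol; both are assumptions. The comparison arm has risk p0 and the intervention arm p0 + f·d.

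The variance of the difference is V = [p0(1−p0)/m + p(1−p)/m + k²(p0² + p²)]/12, with p = p0 + f·d and a two-sided z test at 5%. For Objective 1, p0 = 0.60 and m = 30:

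| f | d (points) | Spurious difference | RR | Type I error |
|---|---|---|---|---|
| 0 | any | 0 | 1.00 | 5% |
| 10% | 10 | +1 point | 1.02 | 5.6% |
| 20% | 20 | +4 points | 1.07 | 14.8% |
| 30% | 20 | +6 points | 1.10 | 27% |
| 30% | 30 | +9 points | 1.15 | 53% |

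Worked line (20%, 20 points): p = 0.60 + 0.20 × 0.20 = 0.64; V = [0.0080 + 0.00768 + 0.01 × (0.36 + 0.4096)]/12 = 0.00195; SE = 0.0441; 0.04/0.0441 = 0.906; rejection rate 14.8%.

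**4. Sign for tracing (Objective 5).** With p0 = 0.30, m = 24 and f = 30%, a gap of +20 points gives 0.36 (RR 1.20, rejection 31%). A gap of −20 points gives 0.24 (RR 0.80, rejection 34%). The negative case is realistic: patients who come back unprompted may never be traced, so traced patients may have the poorer outlook.

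**5. What a receipt-blind rule could cost in power.** Assume 40% uptake and a 15-point effect in recipients only. The expected difference is 0.40 × 15 = 6 points (60% v 66%). V = [0.0080 + 0.00748 + 0.01 × (0.36 + 0.4356)]/12 = 0.00195; SE = 0.0442; 0.06/0.0442 = 1.36; power about 27%.

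**The case against.** The strongest defence is that eligibility still governs entry. The added patients must themselves be eligible. Enrolment begins at the date eligibility is determined (section 9c), and records are reviewed for newly eligible patients in order (section 9d). No passage sets a quota for recipients, ranks them first or removes eligible non-recipients. This stands to the extent that over-representation is something the rule permits once a quota binds, not something it prescribes. It does not make the rule harmless: its stated purpose is to bring in exposed patients who might otherwise be missed, so it is meant to affect who is sampled.

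The concern about exposure is also real. Low early uptake could leave the study badly underpowered, as step 5 shows. But a diluted effect is the effect of the policy as implemented, which section 3c says is being evaluated. Low power does not justify selecting on receipt in one arm.

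Four stronger readings are tempting and not supported:

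- That the effects are biased upward as a matter of fact. The protocol gives no outcome gap, and for tracing even the sign is open.
- That the intervention sample could consist of recipients only. The rule keeps eligible patients who did not receive the intervention, so a worst case built on 100% recipients does not follow from it.
- That the clinician-confirmed route favours intervention clinics. Sections 4b and 4c do not restrict it by arm; unequal use is conjecture. The mismatch with section 8b is real, but it is a separate inconsistency.
- That the single-intervention sub-analysis biases the main result. It comes after the arm comparisons and cannot alter them. The protocol does not say how comparison patients are handled in it, so no size can be given.

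**Conclusion.** The concern holds as a one-arm selection problem. The asymmetry is explicit in the text, it rests on a post-randomisation event, the quotas allow it to change the sample, and section 10c does not correct it. All five cohorts are exposed to it. An upward bias is plausible for Objectives 1–4, where receipt generally requires the patient to attend or stay engaged; for Objective 5 the direction is uncertain.

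The size cannot be determined from the protocol. The Objective 1 range depends wholly on the assumed share shifted and outcome gap: at the low end the harm is slight, at the upper end it is a large part of the planned 15 points, and a larger shift or gap would go beyond it. Confidence is high for the asymmetry and low for any particular figure. It should be settled before enrolment, because it cannot be reliably undone afterwards.

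**What to change.** **Main change.** Delete the receipt-based sentence in section 4. In both arms, enrol from the same record sources, consecutively by eligibility date and regardless of receipt, and analyse by clinic allocation. Record receipt only as a measure of uptake. If extra recipients are wanted for describing uptake, flag them and keep them out of the main comparison. Section 4 should also stop describing full coverage if quotas are to be used.

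**Secondary changes.** Reconcile the clinician-confirmed route in sections 4b and 4c with section 8b and, whichever way that is settled, apply it identically in both arms. Label the single-intervention sub-analysis as non-randomised and exploratory, or restrict it by status at enrolment in both arms.

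**Cost.** The change is to protocol wording and enrolment instructions, and the stated sample size need not change. The real price is fewer exposed patients and lower power if early uptake is low. Spreading each quota evenly over the six-month enrolment window, in both arms alike, would ease this. Section 10b already allows the sample size to be raised, but that helps only so far with 12 clinics per arm. For the 6-point case in step 5, unlimited patients per clinic leaves V = 0.01 × 0.7956/12 = 0.000663, SE = 0.0257, 0.06/0.0257 = 2.33, and power of about 64%.

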## **a. Fast Track ART Initiation Counseling**

Fast track initiation seeks to reduce attrition from chronic care by speeding up the process of treatment initiation for patients who are eligible for treatment and thereby increasing the proportion of treatment-eligible patients who start treatment promptly. For HIV, the goal is to reduce the total number of visits that patients need to complete in order to start treatment and allow patients to initiate treatment over the course of two clinic visits within one week of confirming ART eligibility, with additional counseling provided in the first two routine visits after treatment initiation. The intervention includes a detailed curriculum for the counseling sessions, and providers work with patients to create an individualized adherence plan and ensure post-initiation adherence support[12].

| *Primary outcome:* | Proportion of ART-eligible patients who initiate ART (obtain their first supply of ARV medications) within 30 days of determination of treatment eligibility |
| --- | --- |
| *Eligibility:* | All non-pregnant adult patients who are eligible for ART according to national guidelines (CD4 cell count ≤ 500 or Stage 3 or 4 condition) |
| *Sample size:* | 720 (360 per arm; 30 per cluster) |
| *Data sources:* | HIV counseling and testing (HCT) and CD4 count registers; adherence plans; Tier.Net (South Africa’s national HIV patient care database); counselling registers and other registers or records that document services received prior to ART initiation (including patient record) |

## **b. Adherence Clubs**

Adherence clubs comprise adherent and stable patients on ART who meet at facilities or identified locations in the community, in groups of up to 30 patients every two to three months to receive group counseling, have a clinical assessment, and receive the required supply of pre-packed medications. Adherence clubs are managed by lay staff at the health care facility with support from community health workers. The goal is to keep patients engaged in care and adherent to their medication by providing social support and facilitating medication delivery and treatment monitoring, while also reducing patient visit burden on the clinics[13]. The adherence guidelines SOP provides detailed instructions for establishing and running the clubs and for eligibility criteria and data collection.

| *Primary outcome:* | Proportion of patients eligible for participation in an adherence club who receive all medications within the first 4 months after eligibility |
| --- | --- |
| *Eligibility:* | All adult patients who meet the criteria for being stable on ART (on same ART treatment regimen for at least 12 months; most recent viral load taken in past 6 months, 2 consecutive viral loads undetectable ) OR where a clinician confirms eligibility as a stable patient |
| *Sample size:* | 576 (288 per arm; 24 per cluster) |
| *Data sources:* | Tier.Net; pharmacy records; club register; other registers or records that document services provided during the period of club observation |

